### Randomization

Participants are randomly allocated (1:1) to either the EG (IEME + HIIT, *n* = 53) or the CG (PMR + MCT, *n* = 53). Concealed randomization is conducted by independent employees using version 1.5.2 of the Randomization in Treatment Arms software (RITA, EVIDAT, Kiel, Germany). Randomization follows the minimization procedures according to Pocock and Simon (for review see [30]). The following stratification factors are used: age, sex, MS-phenotype (relapsing-remitting, primary or secondary progressive), disease severity (EDSS score), total fatigue score of the FSMC, levels of cardiorespiratory fitness (peak wattage (Watt_peak_)) and HRQoL (EuroQol-visual analogue scales score (EQ-VAS) [31]) at baseline.

### Study intervention

Treatment in both groups consists of education interventions combined with specific endurance exercise modalities. The highly standardized study interventions are implemented into the participants’ inpatient rehabilitation program, which is tailored to the patient’s additional needs and includes physiotherapy (flexibility, mobility, strength), occupational therapy (ability and adaptation training) and, occasionally, speech therapy, neuropsychological training or counselling by a physician or social worker.

Study interventions differ between groups regarding the applied education approaches and training intensities. Participants in both groups receive an education approach (IEME or PMR) on two days per week and exercise on three days per week on a cycle ergometer (HIIT or MCT) over a period of three weeks (inpatient rehabilitation). The education interventions in both groups (IEME or PMR) are supervised and conducted by MS-experienced and trained occupational therapists (IEME) and physiotherapists (PMR). Exercise intensities are regulated based on peak heart rate (HR_peak_), which is determined in the initial CPET at T_0_. Exercise sessions in both groups include a three-minute warm-up and cool-down at low intensity (50% HR_peak_). The heart-rate-monitored training in both groups is supervised by MS-experienced exercise scientists.

#### Experimental intervention (IEME + HIIT)

##### Energy management education (IEME)

IEME involves face-to-face educational group sessions twice a week for a total duration of 6.5 h over a three-week period. The sessions begin with an individual lecture (1 h), in which participants analyse their energy account, followed by five self-contained IEME group sessions (5 h). Sessions cover the following topics: break management, occupational balance, use of body and environment, simplifying activities and effective communication. Between sessions, participants complete assignments regarding the use of energy conservation strategies and plan the implementation of behavioural changes in their daily routine using self-training tasks. Before discharge from the clinic, the sessions conclude with an individual lecture (0.5 h), in which participants set goals concerning implementation of the learned strategies at home. The IEME-program integrates the principles of patient education, the trans-theoretical model of behaviour change, social cognitive theory, energy conservation strategies and cognitive behavioural techniques, as previously described by Hersche et al. [15]. All sessions are conducted by independent and trained occupational therapists.

##### High-intensity interval training (HIIT)

HIIT consists of physiologically-defined heart-rate-controlled cycling on a cycle ergometer, at 80–100 revolutions per minute (rpm) at 95–100% of HR_peak_ (assessed during the initial CPET). Participants perform five 1.5-min high-intensive exercise bouts at 95–100% of their HR_peak_, followed by active breaks of unloaded pedalling over 2 min, with the aim of achieving 60% of HR_peak_. After completion of the three-week training period, participants will receive an individual training plan to continue the training independently after returning home.

#### Control group (PMR + MCT)

Treatments in the control group represent usual care at the Valens clinic, Switzerland.

##### Progressive muscle relaxation (PMR)

In contrast to IEME, PMR uses enhanced mental relaxation strategies for reducing muscle tension. It consists of a series of standardized relaxation exercises in the supine position. Exercises involve 11 large muscle groups and are combined with deep breathing. Participants attend six group sessions (6 h in total) instructed by trained physiotherapists. Sessions are held twice a week over the three-week intervention period. At discharge participants are encouraged to continue performing the PMR training at home.

##### Moderate continuous training (MCT)

In contrast to HIIT, participants in the MCT perform physiologically defined heart-rate-controlled cycling on a cycle ergometer, at 60–70 rpm at 65% of HR_peak_ (assessed during the initial CPET). Participants execute continuous cycling for 24 min. After completion of the three-week training period, participants receive an individual training plan to continue the training independently after returning home.

#### Booster

Six weeks after discharge from the clinic, all participants receive a reinforcement letter that includes specific information material (a “booster”) to remind them of their individual plans for implementing the energy management strategies/PMR exercises and to reinforce implementation of the exercise training program at home.

### Outcome and assessments

After screening for eligibility and signing the informed consent, anthropometric (height, weight) and demographic data (age, sex, education, employment status, housing situation, smoking status, current medication) are collected, and three other assessments used for stratification are completed after inclusion (enrolment). After randomization to the intervention groups (EG or CG), there are four measurement time-points. A detailed schedule of the measurement time-points and assessments performed is provided in Table 1.

**Table 1 Tab1:**
[figure not shown]
Enrolment, interventions and assessments. T_0_: baseline (entry to the clinic); T_1_: three weeks after baseline (end of intervention and inpatient rehabilitation stay, discharge from clinic); T_2_: four months after baseline; T_3_: six months after baseline; IEME: inpatient energy management education; HIIT: high-intensity interval training; PMR: progressive muscle relaxation; MCT: moderate continuous training; HRQoL: health-related quality of life.

*Cardiorespiratory fitness and fatigue are assessed before randomization, because they are used as stratification factors. Mood is also assessed before randomization because a score of > 11 in the depression subscale of the Hospital Anxiety and Depression scale would mean an exclusion from the study.

**Assessed only for experimental group

#### Primary outcome

The primary outcome of this study is the change in HRQoL over six months (T_0_ to T_3_). HRQoL is assessed using the Medical Outcome Study 36-item Short Form Health Survey (SF-36) [32]. This PROM consists of 36 items, divided into eight subscales, summarized in a Physical Component Scale (PCS) and a Mental Component Scale (MCS), with higher scores indicating better HRQoL [33]. HRQoL is assessed at T_0_ and repeated three weeks after baseline (T_1_), four months after baseline (T_2_) and six months after baseline (T_3_).

#### Secondary outcomes

Secondary outcomes evaluate the benefits of the education interventions and endurance exercise modalities.

##### Indicators of inflammatory activity (matrix metalloproteinase-2 (MMP-2), tryptophan (TRP), kynurenine (KYN), kynurenic acid (KA), quinolinic acid (QA), neutrophil-to-lymphocyte ratio (NLR), interferon-gamma (IFN-γ) and interleukin-6 (IL-6)

Blood samples are drawn at rest by vein puncture from the antecubital vein in a seated position at T_0_ and T_1_ before CPET between 08:00 and 09:00 h. To allow the participant to recover from any inconvenience caused by vein puncture, there is 15 min between sampling and the start of the CPET. Blood cell counts will be assessed using an automated haematology analyser (SYSMEX XN-1000, Norderstedt, Germany), to further determine NLR. Serum samples are centrifuged at 3000 g for 10 min at 4 °C, and the supernatant is stored at − 80 °C until analysis. Serum levels of MMP-2, IFN-gamma and IL-6 are determined using enzyme-linked immunosorbent assay (ELISA) (R&D Systems, Inc., Minneapolis, MN, USA) according to the manufacturer’s instructions. Serum levels of KYN pathway metabolites (TRP, KYN, KA, QA) are analysed by high-performance liquid chromatography coupled with tandem mass spectrometry, as described previously [34].

##### Cardiorespiratory fitness (peak oxygen consumption, peak heart rate, peak wattage)

Cardiorespiratory fitness is assessed through a CPET performed at T_0_ (before randomization, because Watt_peak_ is used as stratification factor) on a cycle ergometer (ergoline 800, ergoline GmbH, Bitz, Germany) and is repeated at T_1_. Individual cardiorespiratory fitness level is monitored by direct and continuous measurements (breath by breath) of peak oxygen consumption (VO_2peak_) by ergospirometry (Jaeger CPX, Germany). VO_2peak_ is defined as the highest VO_2_ value when the following criteria are attained: respiratory equivalent ratio (RER) > 1.10, HR_peak_ within 10 beats min^− 1^ of age-predicted maximum and rating of perceived exertion (RPE) > 8.5, as reported by Wassermann et al. [35].

##### Fatigue

Fatigue is assessed with the German version of the patient-reported FSMC scale [27], which has a proven test-retest reliability. The FSMC has defined cut-off scores to classify mildly, moderately and severely fatigued patients. Cut-off for fatigue is set at total score of 43 and motoric and cognitive sub-scores of 22. Fatigue will be assessed at T_0_ (before randomization because the score will be used as stratification factor) and will be repeated at T_1_, T_2_ and T_3_.

##### Mood

Depression and anxiety are assessed with the Hospital Anxiety and Depression Scale (HADS) [36]. The HADS is a PROM for the assessment of general mental health in adults with physical disorders, consisting of 14 items, seven for anxiety and seven for depression, with higher scores indicating anxiety or depression. HADS is performed at T_0_ (before randomization) and repeated at T_1_, T_2_ and T_3_.

##### Self-efficacy in performing energy conservation strategies

Self-efficacy is assessed with the Self-Efficacy of Perceived Energy Conservation Strategies Assessment (SEPECSA) [37]. This PROM consists of 14 items. Participants are asked to rank how confident they are that they can perform each item, on a scale from 1 (= not at all confident/sure) to 10 (= completely confident/sure). The final score is found by averaging the items, with higher scores indicating greater confidence in self-efficacy. SEPECSA is performed at T_0_ and repeated at T_1_, T_2_ and T_3_.

##### Self-perceived competence in activities of daily living

Self-perceived competence is assessed with the Occupational Self-Assessment (OSA) [38]. This PROM consists of 21 items that represent participation in habits and roles, performance of skills, and volition for participation [39]. Participants rate each item with two 4-point scales to indicate their self-perception of occupational competence (I have a lot of problems doing this – I have some difficulty doing this – I do this well – I do this extremely well) and value for importance (This is not so important to me – This is important to me – This is more important to me – This is most important to me). Following these two steps, clients review their ratings and choose areas of occupational performance and participation that they would like to change. All three steps of the OSA are performed at T_0_. At T_1_, T_2_ and T_3_ the first two steps (self-perception of occupational competence and importance) are repeated.

##### Physical activity

Physical activity level is assessed with a customized and adapted version of the Godin Leisure-Time Exercise Questionnaire (GLTEQ) [40, 41]. Additionally, two customized questions were added: (i) subjective rating of activity level over the last seven days, (ii) scoring of the subjective level of daily physical activities over the last seven days (total time spent in light, moderate and strenuous activities) (see also supplementary file 1). This PROM has been developed for this study and is assessed at T_0_, T_1_, T_2_ and T_3_.

##### Behaviour change in energy management

Behaviour changes in patient’s management of their available energy are assessed with the Behaviour Change in Energy Management-Survey (BCEM-S). This survey has been developed for this study based on the energy conservation strategy survey [42, 43] (see also supplementary file 2) and is sent only to the participants from the EG. The survey evaluates which of the 13 energy conservation strategies have become part of the habits and routines of the IEME participants. The aim is to determine which factors prevent implementation of strategies or cause some strategies to be dropped after a brief period. This will provide important information to further improve the IEME program. This survey consists of eight questions and was created with the Qualtrics Research Core software (Qualtrics, Provo, UT, USA) and is sent as a link via e-mail to the participants at T_2_ and T_3_.

### Safety

Tolerability (safety) of the three-week training and education program for PwMS is monitored by continuous measurement of heart rate and a brief scoring of motivation and exhaustion on a 10-point Likert scale after each session (higher values indicate higher exhaustion/motivation). All training sessions are performed as heart-rate-monitored training. Individual thresholds of the participants are determined through CPET (VO_2peak_) and the participants are advised to train in the respective training zone, preventing overtraining of the participants. Heart rate (beats per minute; bpm) is monitored continuously and the training sessions are supervised by MS experienced exercise scientists. Heart rate during and after the training sessions in both intervention groups should not overstep the pre-defined threshold (of 220 bpm – age). This allows normalization of symptoms within 30 min after the exercise sessions. Moreover, adherence is recorded for each participant.

Although not expected, any severe adverse events during training will be reported directly to the physician on duty and to the ethics committee. This includes: (i) severe cardiovascular and pulmonary diseases (renal failure, hepatic dysfunction, cardiovascular disease) and (ii) severe cardiovascular exacerbations (e.g. arterial blood pressure after Riva Rocci > 240/120, heart rate above the age-predicted maximum of 220 – age).

Regarding the education interventions (IEME or PMR) no specific adverse events are expected. If adverse events occur they will be reported directly to the PI and to the ethics committee.

All participants are inpatients at the Valens clinic, Switzerland for the intervention period. Insurance to cover for harms associated with the study protocol is provided for all participants by the Valens clinic, Switzerland, via the Basler Versicherungsgesellschaft, [name].

### Data management and confidentiality

All data collected from paper forms are archived on a personalised desktop-computer with access to the internal IT-network of the Valens clinic. Data is password secured and with the attachment to the Valens network backups are performed every hour. The original study forms are kept in a closet only accessible to the study staff at the Valens clinic. After study termination, paper forms and electronic files are archived for a minimum of 10 years and then destroyed or deleted. The blood samples are disposed after analysis.

Data generation, transmission, storage and analysis of all health-related personal data and the storage of the biological samples within this project will strictly follow the current Swiss legal requirements for data protection. All health-related personal data captured during this project and the biological samples from participants are strictly confidential and disclosure to third parties is prohibited; coding will safeguard participants’ confidentiality.

### Sample size calculation

The a priori sample size calculation was conducted using G*Power 3.1.9.2 software [44]. It was carried out for the investigation of a between-group difference in the primary endpoint (changes in the HRQoL (PCS and MCS) from baseline to T_3_) in an analysis of covariance model (ANCOVA).

Based on our IEME feasibility randomized clinical trial [16] with four months follow-up of HRQoL, we assume a medium between-group effect size of d = 0.5 on changes in the primary endpoint HRQoL. Level of significance (α) with Bonferroni for multiple comparisons (two primary outcomes) was set at 0.025 and power (1–β) at 0.8. According to Borm et al. 2007 [45], the required sample size for the ANCOVA model was calculated with the formula (1–ρ^2^)**n*. A correlation between participant’s scores at baseline and at T_3_ of ρ = 0.65 was used. The calculation revealed that 90 participants (EG: 45 / CG: 45) would need to be recruited. Based on previous studies that apply similar interventions [16, 22], we have allowed for 18% dropout and plan to recruit 106 participants.

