### Statistical analysis

All analyses are conducted according to intention-to-treat. To determine potential effects of between-subjects factor intervention (IEME + HIIT vs. PMR + MCT) and within-subjects factor measurement time-point (T_0_ to T_3_) and their interaction on primary and secondary outcomes, 2 × 4 mixed ANCOVAs will be applied. As covariates, participants’ baseline score of each specific parameter, EDSS score, MS-phenotype, education, smoking status, occupation, time since diagnosis, age and sex will be included into the model. Post hoc Bonferroni corrected pairwise comparisons will be conducted in case of significant main effect of within-subjects factor measurement time-point. Simple effects analyses will be performed to investigate if groups differ at each measurement time-point. As effect size measures, Eta-square and Cohen’s d will be used in ANCOVA and post hoc analyses, respectively. In addition, bivariate correlation analyses will be conducted to determine potential associations between changes in HRQoL (PCS and MCS) and biomarkers/cardiorespiratory fitness/patient-reported outcomes from T_0_ to T_3_.

Statistical analyses will be performed by a statistician blinded to treatment groups, using SPSS 25® (IBM®, Armonk, NY, USA). A result will be considered significant at *p*-value ≤0.05. Because of multiple testing of the primary endpoint, alpha is adjusted in this case and a *p*-value ≤0.025 will be considered significant.

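### The sample size sets d = 0.5 on the change in HRQoL but applies an ANCOVA factor that is valid only for d in SDs of the T3 score; taken literally, 90 analysable participants give about 63% power per component, not 80%

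*Protocol article*

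**What the plan says.** All the inputs are in the protocol article, mainly under Sample size calculation.

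- **Endpoint.** The calculation is for a between-group difference in "changes in the HRQoL (PCS and MCS) from baseline to T_3" within an ANCOVA model. The Primary outcome section agrees: "The primary outcome of this study is the change in HRQoL over six months".
- **Effect.** "we assume a medium between-group effect size of d = 0.5 on changes in the primary endpoint HRQoL". The source given is the feasibility trial of the education programme, which followed patients for four months.
- **Error rates.** Alpha "with Bonferroni for multiple comparisons (two primary outcomes) was set at 0.025", with "power (1–β) at 0.8". The Statistical analysis section repeats the threshold for the primary endpoint: "a *p*-value ≤0.025 will be considered significant".
- **ANCOVA step.** "the required sample size for the ANCOVA model was calculated with the formula" (1 − ρ²) × n, where a correlation between participants' "scores at baseline and at T_3_ of ρ = 0.65 was used".
- **Result.** 90 participants (45 per arm), raised to 106 for dropout.

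The section gives no SD for PCS or MCS and no difference in points, and it does not say which SD standardises d.

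**The concern.** The factor 1 − ρ² turns the size of a t-test on the follow-up score into the size of an ANCOVA. It compares the ANCOVA residual variance, (1 − ρ²)SD², with the raw variance of the T3 score, SD². It therefore needs a starting n computed with d in SDs of that score.

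The text puts d on the change. The variance of a change score is 2(1 − ρ)SD², which already reflects the correlation between baseline and T3. Multiplying a change-score n by 1 − ρ² credits the same correlation twice and makes the required number too small.

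This paragraph is the article's only justification for the trial's size. If the literal reading is right, each component test has a markedly higher chance of missing the assumed effect than the 20% the plan states, and a non-significant PCS or MCS result would be read as stronger evidence against that effect than it is.

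**Working it through.** **Inputs from the protocol article:** d = 0.5; α = 0.025 per component; power 0.80; ρ = 0.65; 1:1 allocation; 90 to be analysed, 106 to be recruited.

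**Assumptions, not in the document:** a two-sided test, and equal SDs at T0 and T3. Two-sided is the reading that reproduces the stated figure: one-sided 0.025 gives 128 × 0.5775 = 73.9, not 90.

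**1. Reproduce the stated figure.** A two-sample t-test with d = 0.5, two-sided α = 0.025 and 80% power needs 78 per arm (noncentral t), or 156 in total.
- 1 − 0.65² = 0.5775
- 156 × 0.5775 = 90.09, which is the stated 90

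**2. Find the factor that belongs to a change-score d.**
- Variance of the change: 2(1 − ρ)SD² = 2 × 0.35 × SD² = 0.70 SD², so its SD is 0.837 SD
- ANCOVA residual variance: (1 − ρ²)SD² = 0.5775 SD², so the residual SD is 0.760 SD
- Ratio of variances: (1 − ρ²) / [2(1 − ρ)] = (1 + ρ)/2 = 0.5775/0.70 = 0.825

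**3. Power for the effect as written.**
- 0.5 change-score SDs = 0.5 × 0.837 = 0.418 T3-score SDs
- In residual SDs: 0.418/0.760 = 0.550 (equivalently 0.5/√0.825)
- Noncentral t with 45 per arm: power 63.0% (64.4% by the normal approximation)
- Size for 80% power: 156 × 0.825 = 128.7, so about 128 to 130

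**4. Power for the other reading, d in T3-score SDs.**
- In residual SDs: 0.5/0.760 = 0.658
- Noncentral t with 45 per arm: power 79.8%
- The same effect on the change scale: 0.5/0.837 = 0.598, or about 0.60

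**5. Sensitivity of the literal reading (d in change-score SDs).**

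| Varied | Value | Power per component |
|---|---|---|
| ρ, at 90 analysed | 0.5 | 68% |
| | 0.6 | 65% |
| | 0.65 | 63% |
| | 0.7 | 62% |
| | 0.8 | 59% |
| Number analysed, at ρ = 0.65 | 87 (18% lost from 106) | 61% |
| | 106 (no loss) | 71% |

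On this reading neither a different correlation between 0.5 and 0.8 nor complete follow-up restores 80%.

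**The case against.** The strongest reply is that the words about change describe the contrast and not the denominator. In a randomised trial the expected group difference in change equals the expected group difference in the T3 score, so an effect on change divided by a score SD is a coherent d. Nearby text leans the same way: the calculation is framed as an ANCOVA, ρ is defined on raw scores at the two time points, and the analysis adjusts for baseline. On that reading 1 − ρ² is correct and nothing is wrong with 90. Which SD was used depends on the feasibility trial, which is not at hand.

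This stands as far as it goes. A reader might infer from the literal wording that the trial simply has 63% power, and the document does not support that as a flat statement: it never names the standardising SD, and the conversion needs equal SDs at T0 and T3. The reply does not clear the text, though. The natural reading of d on changes is a change-score d, and nothing in the article tells the reader otherwise.

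A reader might also infer that the trial as a whole has a better than one-in-three chance of finding nothing. That does not follow either. The 37% (100 − 63) applies to each component test. If both components have the assumed effect, the chance that at least one is significant is 1 − 0.37² = 86% with independent tests, and about 79% with a correlation of 0.5 between them (both correlations are assumed; the document gives none). The other planned covariates could also add some precision, by an unknown amount.

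Finally, no multiplication is wrong: 156 × 0.5775 is 90. The fault lies in the pairing of effect scale and formula.

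**Conclusion.** The point holds as an inconsistency. The effect size as stated and the ANCOVA formula as stated cannot both stand, so either the power or the assumed effect is misreported.

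- If d = 0.5 is in change-score SDs, as the wording says, the stated 80% overstates power by about 17 percentage points per component, and the required number is short by about 38 to 40 participants.
- If d = 0.5 is in T3-score SDs, the number is right, but the trial is powered for an effect about a fifth larger on the change scale than the text says (0.60/0.50 = 1.2).

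The algebra is certain given equal SDs at T0 and T3 and a two-sided α of 0.025. Which reading the sponsor intended cannot be settled from the article. Either way, a figure the trial relies on is wrong as written and should be corrected.

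**What to change.** Check which SD standardised the effect size taken from the feasibility trial. State it in the sample size section, together with the assumption of equal SDs at T0 and T3. Then do one of the following:

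- **Keep d = 0.5 on change.** Replace 1 − ρ² by (1 + ρ)/2 and restate the power as about 63% per component at 90 analysable participants, with the range over plausible ρ.
- **Restate d = 0.5 as being in T3-score SDs.** Keep 1 − ρ² and the 90, give the effect in PCS and MCS points, and note that it equals about 0.60 on change.

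The cost is a few sentences and a less favourable stated power or detectable effect. Enrolment, design and analysis need not change.

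### Judging PCS and MCS each at a fixed 0.025 is valid, but Holm's step-down rule has the same 5% family-wise error and more power for the second outcome

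*Protocol article*

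**What the plan says.** The Sample size calculation section defines the primary endpoint as "changes in the HRQoL (PCS and MCS) from baseline to T_3", which makes two primary outcomes. Alpha is split "with Bonferroni for multiple comparisons (two primary outcomes) was set at 0.025 and power (1–β) at 0.8". The other inputs are the effect size ("we assume a medium between-group effect size of d = 0.5 on changes in the primary endpoint HRQoL") and the link with baseline ("A correlation between participant’s scores at baseline and at T_3_ of ρ = 0.65 was used"). The result is 90 participants, 45 per arm, raised to 106 for dropout.

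The Statistical analysis section carries the same threshold into the decision: "alpha is adjusted in this case and a *p*-value ≤0.025 will be considered significant". So PCS is judged at 0.025 whatever MCS shows, and the reverse. The article mentions no step-down, hierarchical or other sequential rule. It also does not say whether success needs one component or both.

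**The concern.** Bonferroni spends half of the 5% on each outcome and recovers none of it once one outcome has been shown. Holm recovers it. When the smaller p-value is at or below 0.025, only one hypothesis is left and it can be tested at the full 0.05 without raising the family-wise error above 5%. The two rules differ in one situation only: one component passes 0.025 and the other has a p-value above 0.025 and at or below 0.05. A result of p = 0.001 on PCS and p = 0.03 on MCS, for example, counts as significant on PCS alone under the stated rule, and on both under Holm.

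This matters here because both components are primary, and the Discussion expects the two interventions to act in different domains of quality of life, so a conclusion on each is of interest. The sample size also leaves no reserve above 80% power per outcome.

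**Working it through.** **Inputs from the article.** Alpha 0.025 per outcome, power 0.80, d = 0.5, correlation 0.65 between baseline and T3, 1:1 allocation, 90 evaluable participants. Two inputs are not given: the sidedness of the test, and the correlation between the PCS and MCS test statistics. I took two-sided tests, because only these reproduce the plan's figure, and an assumed correlation of -0.2 to 0.7.

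**1. The plan's own sample size.** A two-sample t-test with d = 0.5, two-sided alpha 0.025 and power 0.80 needs 78 per arm, 156 in total. The ANCOVA factor is 1 - 0.65² = 0.5775, and 156 × 0.5775 = 90.09. The stated 90 reproduces. With one-sided 0.025 or two-sided 0.05 the result would be 128 × 0.5775 = 73.9, which does not.

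**2. Power per outcome at 45 per arm.** The adjusted effect is 0.5 / √0.5775 = 0.658 SD. The noncentrality is 0.658 × √(45/2) = 3.12. The noncentral t distribution gives a = 0.798 at alpha 0.025 and b = 0.870 at alpha 0.05, so b - a = 0.072.

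**3. Independent tests, d = 0.5 on both.**

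- Both shown, Bonferroni: a² = 0.798² = 0.637.
- Both shown, Holm: a² + 2a(b - a) = 0.637 + 2 × 0.798 × 0.072 = 0.752.
- Per outcome, Holm: a + a(b - a) = 0.798 + 0.798 × 0.072 = 0.855.
- At least one shown, either rule: 1 - (1 - a)² = 1 - 0.202² = 0.959.

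**4. Correlated tests.** Simulation of the two t statistics, 2 million draws per case, d = 0.5 on both:

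| Correlation between tests | Per outcome, Bonferroni | Per outcome, Holm | Both, Bonferroni | Both, Holm | At least one, either rule |
|---|---|---|---|---|---|
| -0.2 | 79.8% | 85.9% | 62.2% | 74.5% | 97.3% |
| 0 | 79.8% | 85.6% | 63.7% | 75.2% | 95.9% |
| 0.4 | 79.8% | 84.8% | 67.3% | 77.2% | 92.4% |
| 0.7 | 79.8% | 84.0% | 70.9% | 79.4% | 88.7% |

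**5. Unequal effects.** If the second outcome has a true d of 0.3 (an assumption), its power rises from about 35% to 43-45% over the same correlations. If it has no true effect, the other outcome gains a × 0 plus almost nothing: with independent tests, 0.798 + 0.072 × 0.025 = 0.800, about 0.2 points.

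**6. Family-wise error under Holm.** With no effect on either outcome, the simulated error is 0.0495 at correlation 0 and 0.045 at 0.6. With an effect on one outcome only, the other is falsely declared in about 4.1-4.5% of trials. Both stay below 5%.

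**The case against.** The strongest reply is that nothing here is wrong. Bonferroni is valid, the sizing and the analysis use the same 0.025, and the stated 90 reproduces. The trial gets the 80% power per outcome that it was designed for. All of this stands, and it limits the point to an improvement in efficiency.

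A reader might infer more: that the trial needs significance on both components, so that its real power is only 62-71%. The documents do not support this. The hypothesis in the Background speaks of improved quality of life, and no section makes joint significance the criterion of success. A reader might also infer that p = 0.03 on one component would have to be reported as no effect. The Statistical analysis section defines significance only, and it plans effect sizes as well, so such a result would be non-significant and still reported with its size.

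The gain also depends on effects in both components. The Discussion reports a feasibility result on perceived physical functioning and expects effects in different domains, so unequal effects are plausible. If one component is unaffected, Holm gives almost nothing.

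Two practical objections also hold. The analysis section describes 2 × 4 mixed ANCOVAs with several tests per outcome and does not name one T3 p-value, so the input to Holm must be stated. And fixed Bonferroni keeps test and interval aligned: under Holm, an outcome significant at p = 0.03 has a 97.5% interval that includes zero.

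None of this removes the main fact: at the same family-wise error, Holm never rejects less than the stated rule.

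**Conclusion.** The point holds as an inexpensive gain in power, not as a correction of an error. If both components have the planned effect of d = 0.5, Holm adds about 4 to 6 points of power per outcome (79.8% to about 84-86%) and about 9 to 12 points to the chance of showing both (about 62-71% to 75-79%). A weaker second outcome with d = 0.3 gains about 9 to 10 points. The chance of at least one significant outcome does not change. These figures rest on 45 evaluable participants per arm, the plan's correlation of 0.65, two-sided t-based tests, and an assumed range for the correlation between the PCS and MCS tests, which the article does not give.

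**What to change.** In the Statistical analysis section, replace the fixed threshold for the primary endpoint with wording such as: *The between-group p-values for the change from T0 to T3 in PCS and MCS are ordered. The smaller is significant if it is ≤ 0.025. If it is, the larger is significant if it is ≤ 0.05.* This names the contrast on which the trial is sized, which Holm needs as its input.

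Keep the sample size calculation at 0.025, because that is still the level for the first rejection. Make the change before unblinding: adopting Holm after seeing a p-value of 0.03 would not be credible.

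The cost is this short change of wording, with no added participants or assessments. The downside is that simple intervals no longer mirror the decision exactly. If 97.5% intervals are reported, label them as Bonferroni intervals that may include zero for an outcome significant only at the second Holm step.
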